# **ANNEX-III: Sidaamu Afoo Version Questionnaire**

**QA’MISO II: SIDAAMU AFII GAANO**

**HAWAASI YUNIVERISITE HIKKIMINNUNNA FAYYIMMATE KOLEEJE**

Dagoomu Fayyimmate Rosi Mine

**Gafa Mite: Dawaraanchote Dagoomittete Haja Xa’mi’nanni Borri-xa’mo**

Worada_________ Ollaa________ Dargu Kiiro____________ Koodde_____ Mobayle______________________

| **A.K.** | | **Xa’mo** | **Dawaro** | **Sai** |
| --- | --- | --- | --- | --- |
|  | | Dirikki me’’eho ? | __________wo’mu dirrinni wori |  |
|  | | Teessokki hiikkooti? | - - - 1. Quchumaho       2. Baadiyye |  |
|  | | Adhammete Gara | 1. Leexa 2. Adhantinota 3. shiidhinota 4. tidhantinota 5. baxxitinote |  |
|  | | Ammanokki hiitteeti?  (dawarokki qoqqowi? | 1. Ortodokise 2. Pirotestaante 3. Musiliime 4. Kaatolike 5. Wole xawisi____________ |  |
|  | | Loosu Qeecha? | 1.. Minaama (mini ama )  2. Baatto loossi’re galinoha   1. Mootimmate Loosaasincho 2. Mootimmannita ikkitinokki uurrinshara 3. Halanyaho 4. Rosaanchoho 5. Wole xawisi____________ |  |
|  | | Hiikko ayiddeeti?/ Hiitte gosaati? | 1. Sidaama 2. Wolayitta 3. Amaara 4. Guraage 5. Oromo 6. Wole xawisi___________ |  |
|  | | Rosikki deerri hiikkonneeti?? | 1. Nabbawanna borreessa didandeemma 2. Nabbawanna borreessa calla dandeemma 3. Umi dirimi rosaanchooti 4. 2^ki^ dirimi rosaanchooti 5. 5. 2^ki^ dirimi aleenni rosinote |  |
|  | | Gashshaniki rosi deerri hikkonneeti?  Adhantinota ikkituro,(xa’mo 103 buuxxi) | - - - 1. Nabbawanna borreessa didandaanno  1. Nabbawanna borreessa calla dandaanno 2. Umi dirimi rosaanchooti 3. 2^ki^ dirimi rosaanchooti 4. 2^ki^ dirimi aleenni rosinoho |  |
| **Gaamo-II: Heeshshote Gade Xa’minanni Borri-xa’mo**  Konni woroonni noo borri-xa’mo , xa’mitto/a gedensaanni taaltino dawaro qoqqowi | | | | |
|  | Mereerimunni, ayyirrinore me’’e saate bayiratta barrunni (waa, lowo qaqqo , haqqe, kinchonna gide | | -------- sate |  |
|  | Sigaara wiliishshite egennootta? | | 1. Dee’ni 2. Ee |  |
|  | Maatekki giddo otoottote ayyara gobbara higge fultinohu no ? | | 1. Dee’ni 2. Ee |  |
|  | Keeshshitino busano buuse egennota sase lamallara aleenni ? | | 1. Dee’ni 2. Ee |  |
|  | Jawa shumara ofolata woyte Fula giwanohenni? (fulate qarrissanno) | | 1. Dee’ni 2. Ee |  |
|  | Mundeekki giddo sukkaare noohero buuxi’rootta? | | 1. Dee’ni 2. Ee |  |

**Gaamo III: Amuwu Ilaranna Otoottote Fayyimma Ledo Xaadinohunni Xa’minanni Borri-xa’mo**

| **A.k.** | **Xa’muuwa** | **Dawaaro** | **Sa’i** |
| --- | --- | --- | --- |
|  | Umikki yannara mine assi’roottahu meyikki dirikkiraati? | --------------- dirooti |  |
|  | Lamala agana ikkinokkiha, umo ka’e egennootanni? | 1. Dee’ni 2. Ee |  |
|  | Lamalu aganni gedensanni ilite eggenotanni? | 1. Dee’ni ___________ 2. Ee | sa’i 312 |
|  | Xa’mo303, ee. ikkiro umo ilitta woyite meyikki deerikkiraati? | --------------- dirooti  999……… diafoomma |  |
|  | Me’’e qaaqquulle ilitta? | ___________hige iloomma |  |
|  | Gedeniidi qaaqqo ilitta yannara meyikki dirikkiraati? | ---------- dirooti |  |
|  | Hitoonni ilte egennootta?  (Mittu aleenni doora dandiinanni ) | 1. Qarru noyikkiha iloomma 2. Godowa dadhatenni 3. Udiinnichu kaa’lonni iloomma |  |
|  | Mitto barra sae/(24) saate sae gamaa’mite egennoottanni? | 1. Dee’ni 2. Ee |  |
|  | Sa’u yanna giddo mine ilte egennootanni? | 1. Dee’ni 2. Ee |  |
|  | Gedensiidikki qaaqqo hiikko ilootta? | 1. Mine 2. fayyimmate uurinshara. |  |
|  | Gedensiidi qaaqqo ilittahu gedensaanni, meyikkita mini looso loosa hanafootta? | ----------- barrinni  ……….. lamalate gedensaanni |  |
|  | Godowa dadhite egennootanni? (qaaqqu fula giweennae shiima darga darroonnie, otoottote darroonnie ,danotenni darroonnie, godowi giddo darshinore holaara darroonnie) | 1. Dee’ni 2. Ee |  |
|  | Aganu mundeekki horontanni uurritinoni? (sasu aganni aleenni)? Maatete damboowishsha horoonsi’rittakkinni | 1. Dee’ni 2. Ee |  |
|  | Xa’mo 313, ‘’ee’’ yiittaro, mageeshshi yanna? | ------------- |  |

| **Gaamo -IV: Jajju woy Jirote Amadooshshe**  Konni worooninoo xa’mubba xa’mateni (dandaamiro la’atenni) gara ikkitino dawaro dooni. | | | | | |
| --- | --- | --- | --- | --- | --- |
|  | Maatekki agganno waa afidhannohu hiikkiinniiti? | Baambu waa :   1. Mini giddo baambu waa 2. Hoowete afamanno baambu waa 3. Dagoomu tuqi horoonsi’ranno baambu waa 4. Umme fushshinoonni waa | |  | |
|  |  | Agarooshshe:   1. Garunni agaraminoha 2. Garunni agaraminokkiha | |  | |
|  |  | Buete waa:   1. Garunni agarroonnita 2. Garunni agarroonnikkita | |  | |
|  |  | Daadanno Waa:  1.Lagu/garbu/kofaminoha/xashshuwa/ waa | |  | |
|  | Maatekki sagale loosi’ratenna anga hayishshi’rate horoonsidhanno waa maminni afidhanno? | Baambu waa:   1. Mini giddo baambu waa 2. Hoowete afamanno baambu waa 3. Dagoomu tuqi horoonsi’ranno baambu waa 4. Umme fushshinoonni waa | |  | |
|  |  | Agarooshshe:   1. Garunni agaraminoha 2. Garunni agaraminokkiha | |  | |
|  |  | Buete waa:   1. Garunni agarroonnita 2. Garunni agarroonnikkita | |  | |
|  |  | Daadanno Waa:   1. 1.Lagu/garbu/kofaminoha/xashshu/ waa | |  | |
|  | Way afamanno dargi hiikkooti? | 1. Meessi mini giddo  2.Meessi hoowe giddo  3. Wolu darginni | |  | |
|  | Waa dirri’ne hinganni yanna mageeshsha adhanno ? | 1. Daqiiqa/xu’eessa __________ 2. Dibuuxoommo/a | |  | |
|  | Sa’uta lame lamala giddo way bae barra wo’ma keeshshino? | 1. Dee’ni 2. Eewa 3. Diqaagamannoe | |  | |
|  | Way co’ichimma agarsiisate atewayinni agarrannire assoottori/tari no yite hedatta/o? | 1. Dee’ni ------------------------------------- 2. Eewa | | 4.8 | |
|  | Anganni way co’ichimma agara maa assa noohe?  Wo’manta hedo maareekki | 1. Gafe agatenni 2. Xagga woratenni 3. Hoccootunni ximbiiwaetnni 4. Waa ximbiimbanni meemonni (shaafa/shiimmaadda lubbuwa/etc.) 5. Arrishshote xawaabbinni xagisatenni 6. Mittowa kofatenni/ kuusatenni | |  | |
|  | Maatekki duucha yannara hiittooha shumate mine horoonsidhanno? | WAYINNI XAADINSOONNITA/ XAADINSOONNIKKITA   1. Baamba fanne horoonsi’nannita 2. Baambaho xaaddino way maashine 3. Ummooni balera waa horoonsi’ra 4. Base baalate waa horoonsi’ratenni 5. Shumate mini waa hiissine horoonsi’nanniro diafoommo/a?   BALE UMME QIXXEESSINOONNI SHUMATE MINE   1. Ayyare e’anno shumate mine 2. Bale umme suudinsoonni kinchinni 3. Bale umme afoo tu’noonnikkita 4. Mu’roote horonsi’nanni shumate mine. 5. Waa baaldete worreenna 6. Gottiima shumate mine   7.Injiinowi dino/dubbu giddo/xawoho | |  | |
|  | Tenne owaante woloota maate ledo horoonsidhinanni? | 1. Dee’ni 2. Eewa | |  | |
|  | Ate maate ledo mageeshshi mannaati konne shumate mine horoonsidhinannihu? | 1. 10 nni ajanno 2. 10 woy hakkuy ali 3. Afoommori/mari dino | |  | |
|  | Hakku shumate mini afmannohu hiikkooti? | 1. Mini giddo 2. Meessi hoowe giddo 3. Wole dargaati | |  | |
|  | Maatekki sagale loosi’rate hiittee gaaze horoonsidhanno? | 1. Korreentete wolqa 2. Du’nantanno gaaze 3. Kalaqamu gaaze 4. Addi addi keemikaalla 5. Laamba 6. Qitiissinoonni haqqe (kasale) 7. Haqqe 8. Kashee/hayissotenni 9. Gidu damatenni 10. Saadate obbinni 11. Sagale diloosi’neemmo | |  | |
|  | Sagale loosi’nannihu gallaniwaati, baxxitino kifileeti/ mini gobbaanniti? | 1. Mini giddooti 2. Baxxino mineeti 3. Barandahooti 4. Wolewaati | |  | |
|  | Sagale loosi’rate horoonsidhinanni baxxino mini noo’ne? | 1. Dinonke 2. Eewa | |  | |
|  | Minu galtinannihu ayeho? | 1. Ko meessiho 2. Baante gallanniho 3. Fiixunniho 4. Elunniho 5. Wole hee’riro xawisi_________________ | |  | |
|  | Konni mini giddo gonxanni kifilla me’’e no? | --------Kifilla no | |  | |
|  | Minu giddoydo iimiidi raga(korniise) mayinni biifinsoonniho? | 1. Kalaqamu haqqinni (biinfori dino, sabbunni,nna kandoonni sabbinni) 2. Calla anfi gede assinnoonniha (xu’minsoonnikki saattinni/plastic shara, shomboqqotenni/leemmichunni, haqqu xaawulinni, and komborsaatunni) 3. Xu’minsoonnikorniise (siwiilunni/culku siwiilinni, haqqunni,alumineemetnni/simintotenni | |  | |
|  | Mini uulliidi loosaminohu mayinniiti? | 1. Kalaqamunni noo gedeenni nooho (baatto/ bushshaho) 2. Safo tunge doogo hunnoonniho (haqqu xaawula, nna shomboqqotenni/ leemmichunni) 3. Xu’minsoonni mine (shakilunni) (haqqu xaawulinni xu’minsoonniha, uullano iimano shakila, simintotenni, alumineemetenni, uulla karranni shara(minxaafe) | |  | |
|  | Minu anni / ati saadate hoshsho, baatto hawuurranni saadanna lukkuwa ceo noosiho? | 1. Dee’ni 2. Eewa | |  | |
| - - 1. 4 | Aliidi saada giddonni minu annihu mageeshshaati?  Mitturi nokki ikkiro(00) wori.  95 tu woroonna aleenni ikkiro (95) wori.  Kiiro anfonikkiha ikkiro(98) wori | 1. Saadanna bootta_______________ 2. Wole saada______________ 3. Farado/harre/gaangootta ____ 4. Gaala________ 5. Me’’e _________ 6. Ge’reewo _________ 7. Caacurre/ lukkuwa ______ 8. Diishshote koshsha | |  | |
| - - 1. 421 | Saada galtannowi baxxino dargi noo’ne? | 1. Dee’ni 2. Eewa | |  | |
| - - 1. 422 | Maate’ne giddo loosi’nanni baatto afi’nohu no? | 1. Dee’ni ------------------------------------- 2. Eewa | | 4.24 | |
| - - 1. 423 | Minu annira me’’e hekitaare ikkitannoti loossi’nanni baatto noosi? | ___________Hekitaare | |  | |
| - - 1. 424 | Konni worooni noori giddo mini’ne giddo afamanohu hiiko neeti? (mittete aleeni doora dandiinanni) |  | Eewa(1) | Dino (0) |  |
|  |  | 1. Korreente---------- 2. Raadoone ----------- 3. Telewishiine -------- 4. Mine silke---------- 5. Kompiitere ---------- 6. Mitore qiissanno udiinnichi --- 7. Xarapheezzu -------- 8. Barcimu ------------- 9. Shiwote daallasi---- 10. Korreentete wolqanni sagale raisi’nanni mixashsho ----- 11. Laambunni/shaamu/ ------ 12. Faanoose------------- |  |  |  |
|  | Maatekki giddo togoo udiinni no: |  | Ee  (1) | Dino  (0) |  |
|  |  | 1. Tolobishiine -------- 2. Bilbilu------ 3. Shalleette------------ 4. Xexxerrisu------ 5. Saadate gaare- 6. Kaameelu/ hogowi kaameeli --------- 7. Yowolo motor nooti----- 8. Sasu goommi baajaaje ------------ |  |  |  |
| - - 1. 426 | Maatekkira baankete akkowaante kiiro noonsa? | 1. Dinonsa 2. Eewa | |  | |
| - - 1. 427 | Maatekki giddo shiimmaadda daddalu uurrinsha akkowaante kiiro noonsa? | 1. Dee’ni 2. Eewa | |  | |
|  | Maate’ne giddo sigaara wiliishshaahu barrunni me’’e higeeti?  Barrunni/lamalatenni/ aganunni/ dirunni / takkonta? | 1. Barrunni 2. Lamalatenni 3. Aganunni 4. Aganunni mitteege 5. Takkonta | |  | |

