**Part III: Respondents’ Obstetrics and Gynecologic related factors**

| **Sr. No.** | **Questions** | **Choices of response** | **Skip to** |
| --- | --- | --- | --- |
|  | What was your age when you married for the first time? | --------------- years completed |  |
|  | Did you have a history of pregnancy terminated before seven months? | 1. No 2. Yes |  |
|  | Did you give childbirth after seven months of pregnancy? | 1. No 2. Yes | If no, go to Q312 |
|  | If yes, what was your age at first delivery? | --------------- in years  999……… don’t know |  |
|  | How many children you delivered? | ___________no. of delivery |  |
|  | What was your age at last delivery? | ---------- years |  |
|  | Which mode of delivery have you ever faced?  More than one option is possible | 1. Spontaneous vaginal delivery 2. Cesarean delivery 3. Assisted instrumental delivery |  |
|  | Have you ever experienced labor that lasted more than one day and night (>24hrs)? | 1. No 2. Yes |  |
|  | Have you ever given birth at home (previously)? | 1. No 2. Yes |  |
|  | Where did you deliver your last child? | 1. At home 2. Health facility |  |
|  | When did you start household work after delivery of your last baby? | ----------- days  ……….. weeks after delivery |  |
|  | Do you have a history of pelvic surgery (episiotomy, hysterectomy, trauma, tumor removal) | 1. No 2. Yes |  |
|  | Is your menstrual cycle stopped permanently (more than 3 cycles)? Without contraceptive use? | 1. No 2. Yes |  |
|  | If yes for Q-313, for how long? | ------------- |  |

| **Part-IV: Study participants wealth Index**  Ask (and observe when possible) the following questions one at a time and write the response on the space provided or encircle the appropriate response from the options listed. | | | | | |
| --- | --- | --- | --- | --- | --- |
|  | What is the main source of drinking water for members of your household? | Piped water:   - 1. Piped into dwelling   2. Piped to yard/plot   3. Public tab/standpipe   4. Borehole | | |  |
|  |  | Dug well:   1. Protected well 2. Unprotected well | | |  |
|  |  | Water from spring:   1. Protected spring 2. Unprotected spring | | |  |
|  |  | Surface water:   - - - 1. River/lake/pond/stream/dam | | |  |
|  | What is the main source of water used by your household for other purposes such as cooking and handwashing? | Piped water:   1. Piped into dwelling 2. Piped to yard/plot 3. Public tab/standpipe 4. Borehole | | |  |

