**PART-V: POP-SS**

**Direction**

The following seven questionnaires are standard tools used to measure prolapse symptoms. Each item/question has 0 to 4 possible response scales. Inform the participant how to give a rate for each item based on how often she felt the prolapse symptom in the last four weeks (Put ‘X’ in the right box under each response scale).

Dear participant, please tell me how often did you feel the following POP symptoms in the last four weeks? (Please give the rating scale as follows: 0= never felt symptom in the last four weeks, 1= occasionally, 2= sometimes, 3= most of the time and 4= all of the time)

| **S.no** | **POP-Symptoms** | **0**  never felt symptom in the last four weeks | **1**  occasionally | **2**  sometimes | | **3**  most of the time | **4**  all of the time |
| --- | --- | --- | --- | --- | --- | --- | --- |
|  | A feeling of something coming down from or in your vagina? |  |  |  | |  |  |
|  | An uncomfortable feeling or pain in your vagina which is worse when standing? |  |  |  | |  |  |
|  | A heaviness or dragging feeling in your lower abdomen/tummy? |  |  |  | |  |  |
|  | A heaviness or dragging feeling in your lower back? |  |  |  | |  |  |
|  | A need to strain (push) to empty your bladder? |  |  |  | |  |  |
|  | A feeling that your bladder has not emptied completely? |  |  |  | |  |  |
|  | A feeling that your bowel has not emptied completely? |  |  |  | |  |  |
|  | Which of the symptoms above (questions 1–7) causes you most bother? | ……………. | | | | | |
|  | For how long have you felt one of the most chronic symptoms? | ……… | | | | | |
| **Patient Global Impression of Change questionnaire**  Ask the following questions only at end-line assessment (after intervention). Both the control and interventional group participants will be asked at the end of six months. | | | | | | | |
|  | How do you Perceive the change in prolapse since the start of the intervention? | | | | 1= Very much improved  2= Much improved  3= Minimally improved  4 = No change  5= Minimally worse  6= Much worse  7= Very much worse | | |

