**Gaamo-V: Otootto Gobbara Higge Fulturo Leellanno Malaatta Buunxanni Borri-Xa’mo**

**Hajajo:** Konni woroonni shiqqino lamala borri-xa’mo illachishshannohu otootto gobbara higge fultino amuwira xa’minanninna bikkinanni xa’muuwaati. Doorshu noohu ( 0) kayse 4 geeshshaati. Muxxe tenne xiinxallo beeqqaancho, sa’u shoole lamallara me’’e hige malaatu macciishshamihero ballo eeggatena kulie? (keennanni gari : 0= horontanni dileellinoe malaatu sa’u shoole lamallara,, 1= keeshshe, 2= sae sae 3=roore yannanna 4= wo’ma woyte)

| **A.k** | **Leeltanno malaatta** | | **0**  Horontanni dileellanno | **1**  Keeshshe keeshshe | **2**  Sae sae | **3**  Roore yanna | 4  Wo’ma yanna |
| --- | --- | --- | --- | --- | --- | --- | --- |
|  | Ikkinorichi otoottote widoonni hige daynoha lawe macciishshaminoheni? | |  |  |  |  |  |
|  | Otootto xissitannohenni roorenkanni uurrutta yannara ? | |  |  |  |  |  |
|  | Mudukku woroonni ayirrannoherichi macciishshamannoheni? | |  |  |  |  |  |
|  | Hallikkira wori adda duunaminori woy ayirrinori macciishshame egenninoheni? | |  |  |  |  |  |
|  | Way shuma daggukkinni niixissannoheni? | |  |  |  |  |  |
|  | Way shuma gooffinokkiha lawe macciishshamannoheni? | |  |  |  |  |  |
|  | Jawiidi shuma gooffinokkiha lawe macciishshamannoheni? | |  |  |  |  |  |
|  | Aleenni xawinsiri giddo roorenkanni mittinsino qarri hiikkonneeti? (xa’mo 1–7) geeshsha | | ……………. | | | | |
|  | Mageshshi yanna mittu malaati macciishshamihe roorenkanni seeda yannara? | | ……… | | | | |
| **Kalqete Dhiwamaasinetenni Afi’nanni Babbaxxitino Borri-Xa’mo**  Konni woroonni no borri-xa’mo xa’minannihu goofimarchohooti. Xa’minannihu dhibbu malaati nooriranna nookkihuraati. Xa’minanni yanna lewu(6) agani gedensaanniiti | | | | | | | |
|  | Xagisi’ra hanafittankunni may soorro leeltinoha lawannohe? | 1= lowo geeshsha huroomma  2= woyyate  3= dhibbu ajanni ha’rinoe  4 = mitte soorro dino  5= shiima geeshsha xissanni nooe  6= xissanni nooe  7= lowo geeshsha xissanni nooe | | | | | |

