**SIIMU XAADOOSHSHI YANNARA.**

- Otootto fultanno yannarano siimu xaadooshshi assa qarra diabbitanno woy qarra dileddanno.
- Bisu moolannokki gede qufisannoricho horoonsi'ra(sirote bisi kifilera)

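### Two obstetric items in the Sidaamu Afoo questionnaire do not match the English form, so mode of delivery and history of pelvic surgery may be misclassified

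*Protocol*

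**What the plan says.** The English form (Annex II, Part III) offers three answers on mode of delivery, and more than one may be chosen: "1. Spontaneous vaginal delivery 2. Cesarean delivery 3. Assisted instrumental delivery". In the Sidaamu Afoo form (Annex III, Part III) the first two are "1. Qarru noyikkiha iloomma 2. Godowa dadhatenni". Five items later the English form asks "Do you have a history of pelvic surgery (episiotomy, hysterectomy, trauma, tumor removal", and the Sidaamu Afoo stem is "Godowa dadhite egennootanni", followed by four examples in brackets.

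Both variables are risk factors in Paper II (Study Variables) and covariates in Paper III (Variables). Paper IV (Variables) lists mode of delivery but not pelvic surgery.

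Paper II, Data Collection Tools and Procedures, says that the socio-demographic, lifestyle and obstetric sections were written in English and will be translated by a native speaker and an expert in maternal or reproductive health. It states no back-translation for them. Back-translation is stated for POP-SS (Paper I), for PFDI-20, ICIQ-SF and P-QoL (Paper II), for PGIC (Paper III) and for PGI-I (Paper IV). Data Quality Assurance in Paper II adds a pretest of the tools other than POP-SS on 41 women, with unclear items to be revised.

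**The concern.** The English mode question classifies births by route and assistance. The first Sidaamu Afoo option appears to classify them by ease. If so, a woman with a long or hard vaginal birth and no instruments has no fitting answer, while a woman with an uncomplicated caesarean could also choose option 1. Any such loss would not be random. It would fall on difficult labours, and the literature review names prolonged labour as a risk factor for prolapse.

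The surgery stem raises a separate problem. If it is heard as a question about caesarean, women with no other operation enter the exposed group. The literature review treats vaginal birth as carrying more prolapse risk than caesarean, and hysterectomy as a risk factor. Mixing caesarean-only women into the surgery group would then pull a raised odds ratio for pelvic surgery towards 1. For mode of delivery the direction of bias cannot be stated without knowing which births are lost or moved.

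**Working it through.** No figure in the plan bears on this point, so the check sets the two language versions side by side. Word meanings come only from places where the protocol gives both languages.

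**Option 1 of the mode question**

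| Element | Sidaamu Afoo text | English counterpart |
|---|---|---|
| *qarr-* | POP-SS follow-up item, Annex III Part V: "roorenkanni mittinsino qarri hiikkonneeti" | "causes you most bother" |
| *qarr-* | Leaflet on intercourse, Annex IV: "siimu xaadooshshi assa qarra diabbitanno woy qarra dileddanno" | the act neither harms nor worsens the prolapse |
| *nokki* | Livestock item, Annex III Part IV: "Mitturi nokki ikkiro(00) wori" | if none, enter 00 |
| *-kki-* | Well types, Annex III Part IV: *agaraminoha*, *agaraminokkiha* | protected, unprotected |

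So *qarr-* marks trouble or a problem, and *-kki-* marks negation. The exact form *noyikkiha* has no direct parallel, so its meaning is inferred from *nokki*. Together the option reads about as: I delivered with no trouble. Neither the vagina nor the birth canal is named.

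A route wording was available. Under pregnancy and childbirth, where the English leaflet speaks of vaginal delivery, the Sidaamu Afoo leaflet (Annex IV) has the route phrase *sirote kifile widoonni*. The fistula screen (Part VIII) renders vaginal birth in a third way, *Keeraancho ila*, also without those anatomical words. The form therefore has no single term for this exposure.

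**Pelvic-surgery item**

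1. The caesarean option is *Godowa dadhatenni* and the surgery stem begins *Godowa dadhite*: the same noun and the same verb root.
2. *Godow-* stands for the abdomen in Part IX, where it renders abdominal striae.
3. The leaflet's entry on previous pelvic surgery puts *Mudukku woroonni* before this phrase. The questionnaire stem leaves it out.
4. In POP-SS item 3, *Mudukku woroonni* stands opposite the lower abdomen. The qualifier would narrow the stem, but would not by itself rule out caesarean.
5. The four bracketed examples match the English list (episiotomy, hysterectomy, trauma, tumour) in number and order. None is a caesarean, and nothing says that a caesarean does not count.

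**Would the planned checks detect this?** The pretest covers 5% of the sample (0.05 × 816 = 40.8, so 41 women) and looks at clarity and interview time. A phrase can be perfectly clear to respondents and still mean something different from the English. Back-translation is the step that tests equivalence, and it is not stated for this section.

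**The case against.** The strongest reply is that option 1 may simply be idiom. Beside a caesarean option and an instrumental option, 'delivered without trouble' may be how respondents ordinarily hear normal birth. The fistula screen's different but equally non-anatomical wording is compatible with that. The documents cannot settle the matter, and this part of the objection stands.

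The safeguards are also real. The surgery item carries its examples, fluent interviewers ask the questions face to face after two days of training, and unclear items are to be changed after the pretest. The form is still described as to be translated, so the annexed text may not be final. Labour beyond 24 hours has its own item, vaginal birth is asked again in Part VIII, and women who report both caesarean and surgery can be identified. Finally, the definition of pelvic surgery in Paper II (Data Source and Measurement) is illustrative and does not expressly exclude caesarean. These points reduce the risk. They do not remove it, because none compares the Sidaamu Afoo meaning with the English.

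Three stronger readings are tempting and are not supported:

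- **The two variables are miscoded.** The response codes match the English form, and how women will answer is not known. Only a risk of misclassification is shown.
- **Nothing in the plan could catch it.** The pretest might. What is missing is a stated equivalence check.
- **A definite bias can be quoted.** Suppose caesarean-only women are 3 to 8% of the sample, women with true pelvic surgery 10 to 20%, prevalence in the reference group 56%, and odds ratios 2.0 for surgery and 0.5 for caesarean. Prevalence is then 0.718 with surgery and 0.389 with caesarean only. If every caesarean-only woman answers yes, the mixed group has (20 × 0.718 + 3 × 0.389)/23 = 0.675, an odds ratio of about 1.63, or at the other extreme (10 × 0.718 + 8 × 0.389)/18 = 0.572, about 1.05. The exposure frequencies and odds ratios are not in the protocol. The nearest prevalence figure, 56.3%, is described in the literature review as grade two or worse, whereas Paper II counts stage I or more. The universal yes also ignores the bracketed examples. The range shows direction only.

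**Conclusion.** The point holds as a translation mismatch that may misclassify two variables. The overlap between the surgery stem and the caesarean option is visible on the page. The reading of option 1 is an inference from parallel text and depends on confirmation by a native speaker.

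The main exposure is in the Paper II risk-factor estimates. Covariate adjustment is affected in Paper III for both items and in Paper IV for mode of delivery only. A reader might infer that the trial's main result is at risk. It is not: the between-arm t-test of POP-SS change (Paper III, Data Management and Analysis) uses neither item. The size of any misclassification cannot be derived from the documents.

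**What to change.** 1. Word option 1 as birth through the vagina without instruments, whatever its difficulty, building on the leaflet's route phrase. Use the same term in the fistula screen.
2. Add the leaflet's qualifier to the surgery stem, keep the four examples, and state that a caesarean alone does not count, since the mode question already records it. Put the same statement in the English item and in the definition under Data Source and Measurement.
3. Back-translate Part III, as is already planned for the symptom and quality-of-life tools, and have a native speaker confirm both readings.

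The cost is two reworded lines, one added exclusion statement, consistent use of the new term and one back-translation before printing. After the 816 interviews, the separate items on labour length and vaginal birth would allow only a partial repair.
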